#### Secondary Outcomes

Change in motor performance after training JTT is also assessed after two blocks of training (Figure 1). Changes in JTT after stimulation + training are calculated as: [(JTT post-stimulation + training – JTT pre-stimulation)/(JTT pre-stimulation)] × 100.

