Likewise, the effects of RPSS on synaptic activity or concentration of neurotransmitters are unknown. γ-Aminobutyric acid in the sensorimotor cortex has been implicated in the processing of afferent input. For instance, in healthy subjects, GABA concentrations evaluated with magnetic resonance spectroscopy predict changes in perceptual outcome after afferent, tactile stimulation of fingertips (33). In rats, GABAergic inhibition modulates responsiveness to afferent stimulation of the forepaw (34). The GABA concentration or activity in M1 may influence responsiveness to RPSS. Furthermore, RPSS may also increase or decrease GABA levels in the cortex. Until now, these hypotheses have not yet been tested.

The primary goal of this study is to compare the effects of a single session of RPSS on motor performance and motor learning in subjects with stroke in the subacute (EARLYgroup) and chronic (CHRONICgroup) phases with mild upper limb motor impairments. We hypothesize that enhancement of motor performance and motor learning by RPSS will be significantly greater in subjects in the CHRONICgroup than in subjects in the EARLYgroup, when exposed to the same experimental paradigm. In addition, we compare the effects of a single session of RPSS on cerebral perfusion, changes in the BOLD effect, and on GABA levels changes in ipsilesional and contralesional M1. Our hypothesis is that changes in these outcomes will be significantly greater after RPSS in subjects in the chronic, than in the early stage.

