A single session of RPSS has been shown to improve motor performance in the absence of training (19–22, 47) and to enhance effects of training (11, 16, 18, 22). In session 3 (Figure 1), patients are initially familiarized with the JTT by performing each task once in two blocks of practice. Then, baseline assessments are performed. After suprasensory RPSS or subsensory for 2 h, the JTT scores and strength are reassessed. Then, the subjects undergo two blocks of training of tasks of the JTT under the supervision of a rehabilitation professional blinded to the type of stimulation received (22). During motor training, subjects are instructed to perform the JTT tasks that they can complete as fast as possible. Two blocks of training are administered. In each block, each task is performed once. JTT performance is reassessed after training.

Adverse events are monitored during and immediately after the stimulation. Studies included in a systematic review did not report any serious adverse events (6). Two studies described contact dermatitis on the skin under the electrode. If hyperemia is identified after stimulation, this will be reported as an adverse event. If it resolves spontaneously in 30 min, no further action is taken. If there is itching or persistent hyperemia, a topical corticoid cream may be used. In all three centers, the visits and experiments take place inside hospitals with medical resources. A specific insurance policy for clinical trials was taken for financial protection of the sponsor and researchers.

The visual analog scale (VAS) assessed before and after stimulation and after training, to grade sleepiness, fatigue, and anxiety (42).

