### Outcome Measures

#### Primary Outcome: Change in Motor Performance After Stimulation

The primary outcome is change in the JTT performance after stimulation, compared to baseline (Figure 1): (JTT pre-stimulation – JTT post-stimulation/JTT pre stimulation) × 100. The task of copying a sentence is not performed. Previous studies showed that RPSS can enhance JTT performance and motor learning in subjects in the chronic phase after stroke (20, 29).

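### The only after-training JTT outcome combines stimulation and training, so taken alone it does not isolate the motor-learning effect named in the primary goal

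*Protocol article*

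**What the plan says.** All references are to the protocol article.

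- **Goal (Introduction).** "The primary goal of this study is to compare the effects of a single session of RPSS on motor performance and motor learning". The hypothesis covers both parts: "We hypothesize that enhancement of motor performance and motor learning by RPSS will be significantly greater in subjects in the CHRONICgroup", compared with the early group.
- **Measurements (Interventions).** JTT is taken at baseline, then again before any training: "After suprasensory RPSS or subsensory for 2 h, the JTT scores and strength are reassessed". Two training blocks follow, and then "JTT performance is reassessed after training". The same section treats improvement without training and a boost to the effects of training as two separate findings of past studies.
- **Primary outcome.** The printed formula ends "JTT pre-stimulation – JTT post-stimulation/JTT pre stimulation) × 100". A bracket is missing. The evident meaning is the fall in JTT time from before to after stimulation, as a percentage of the value before stimulation.
- **After-training outcome (Secondary Outcomes).** "Changes in JTT after stimulation + training are calculated as: [(JTT post-stimulation + training – JTT pre-stimulation)/(JTT pre-stimulation)] × 100".
- **Analysis (Statistical Analysis).** Changes in JTT are compared with intervention and phase after stroke as factors. Neither this section nor Outcome Measures names a contrast between post-stimulation and post-training JTT.

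**The concern.** Motor learning, in this design, is what patients gain from the training blocks. The natural reference is the JTT taken just before training, which every patient has. The printed outcome uses the value before stimulation instead, so the whole immediate effect of stimulation is carried into it.

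If this outcome is used to answer the learning part of the goal, two errors are possible. An immediate effect that merely persists could be taken for better learning. A true effect on learning could be hidden by an opposite immediate effect.

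The risk is concrete here. The Introduction cites a subacute study in which subsensory stimulation did better than suprasensory, and the Discussion warns that subsensory stimulation may be active in the first weeks. The authors thus allow for an immediate effect that differs by phase, and any such difference passes into the after-training comparison between phases.

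**Working it through.** **Inputs.** Let B be JTT before stimulation, P after stimulation and T after training, all from Interventions. The plan gives no expected value for any of them, so there is no planned figure for this outcome to reproduce. The sample size is used below only to set the scale of a simulation: 68/0.95 = 71.6, which rounds up to the stated 72.

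**Step 1: identity.**

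- Primary outcome: (B - P)/B
- Training gain on the same denominator: (P - T)/B
- After-training outcome: (T - B)/B = -[(B - P)/B + (P - T)/B]

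This holds for each patient, so it also holds for group means and for the intervention-by-phase interaction. Apart from sign, the after-training contrast is the primary contrast plus the training-gain contrast.

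**Step 2: same training gain, different outcome** (illustrative times, not from the documents).

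- Arm 1: B = 60, P = 54, T = 54 × 0.95 = 51.3. Outcome (51.3 - 60)/60 = -14.5%.
- Arm 2: B = 60, P = 60, T = 60 × 0.95 = 57. Outcome (57 - 60)/60 = -5.0%.
- Difference 9.5 points, although T/P = 0.95 in both arms. On the common denominator the gains are 2.7/60 = 4.5% and 3/60 = 5.0%.

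**Step 3: different training gain, same outcome** (illustrative, B = 100).

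- P = 88, T = 88: outcome -12%, training gain 0.
- P = 98, T = 88: outcome -12%, training gain 10/98 = 10.2% of P.

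**Step 4: how often it would mislead if read as learning.** The article prints no effect size or SD. Back-solving from 34 against 34, two-sided 5% and 80% power gives (1.960 + 0.842) × √(2/34) = 0.68 SD. Two arms of 34 were simulated 20,000 times per setting and compared by t-test, with stimulation change and training gain drawn independently. The SD of training gain was set at 0.25, 0.5 and 1.0 times that of the stimulation change. Entries are the share of trials with p < 0.05.

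| Truth | Outcome tested | 0.25 | 0.5 | 1.0 |
|---|---|---|---|---|
| Stimulation effect 0.68 SD, no effect on training gain | After-training, as printed | 76% | 69% | 50% |
| Same | Training gain | 5% | 5% | 5% |
| No stimulation effect, effect on training gain 0.68 of its SD | After-training, as printed | 10% | 23% | 50% |
| Same | Training gain | 79% | 79% | 79% |

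When a stimulation benefit was offset by an equal loss of training gain, the printed outcome was significant in about 5% of trials.

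**The case against.** The strongest reply is that the outcome is honestly labelled. It is called a change after stimulation plus training, not motor learning, and the article presents RPSS as an add-on to motor training. Total improvement from a randomised baseline is a sound target for that purpose. Read this way, the 50% to 76% in the table are true positives. This stands, and is why the measure should be kept.

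A reader might go further and infer that the trial cannot show an effect on learning. The documents do not support that. All three JTT values are collected, and the after-training outcome with its sign reversed, minus the primary, is exactly (P - T)/B. What is lacking is a stated contrast, not the information.

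A reader might also object that the two JTT outcomes share baseline error. With equal, independent errors they correlate at 0.5, but the primary and the training gain share the error in P and correlate at -0.5. Correlation favours neither choice.

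Lastly, only a condensed article is shown, and the full protocol or analysis plan may name a further contrast. That is possible. The point does not rest on silence alone, however: the article prints an explicit formula for its one after-training outcome, and that formula does not match the learning part of its own goal.

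**Conclusion.** The point holds in a limited form. The after-training JTT outcome estimates the combined effect and, on its own, does not separate an effect on training gain from a persisting immediate effect, although learning is part of the primary goal and hypothesis. This follows from the identity and needs no assumption beyond reading the primary formula as evidently meant.

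The size is illustrative. The 9.5 points come from invented times, and the simulated rates rest on a back-solved effect, assumed SD ratios and independence. Those rates count as errors only if the combined outcome is read as learning.

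The primary outcome, its model and the sample size are not affected. The matter is worth settling before results are seen, because a learning contrast chosen afterwards would be post hoc.

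**What to change.** 1. Keep the present measure and name it the combined stimulation-plus-training effect.
2. Add a prespecified training-gain outcome: the unadjusted change from post-stimulation to post-training JTT, compared with intervention, phase and their interaction. Choose one scale in advance. The log ratio of T to P treats equal proportional gains as equal. (P - T)/B × 100 adds exactly to the primary. Step 2 shows that they can differ slightly (equal gains against 4.5% and 5.0%).
3. Base any statement on motor learning on that contrast.
4. Use a model that adjusts for post-stimulation JTT at most as a sensitivity analysis. That value is measured with error, after randomisation, and is affected by treatment.
5. While editing, restore the missing bracket in the primary formula and give both JTT outcomes the same sign.

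**Cost.** One more analysis on values already scheduled, with no new visits or patients. The training gain is probably smaller and noisier than the combined effect, and patients with a large immediate gain may have less room to improve. Because all patients train, the contrast also includes any fading or build-up of the stimulation effect during the training period, which should be said when it is reported.

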##### Hand Strength

Lateral pinch and grasp strength are measured with a dynamometer (Saehan grip) according to a protocol with established validity (44). In Session 3 (Figure 1), patients are initially familiarized by performing lateral pinch and grisp strength once, using the dynamometer. Then, for outcome assessments, five trials of pinch and handgrip are performed before and after stimulation (Figure 1). During each trial, the patient is instructed to perform the movement for 5 s. The average of five trials is calculated. Improvement in pinch strength after RPSS was previously described in separate studies that included patients in the subacute (8) and chronic (39) post-stroke phases (44).

##### Imaging Outcomes

Before and after RPSS, GABA+ (GABA plus coedited macromolecules) levels, CBF assessed with arterial spin labeling, and task-related BOLD fMRI activation are assessed at HIAE. MRI is performed before and after suprasensory RPSS or subsensory on a 3T Magnetom PRISMA scanner (Siemens Medical Solutions, Erlangen, Germany) using a 64-channel 1H receive-only head coil, without contraindications.

A standard questionnaire is used to assess potential exclusion criteria for MRI (Supplementary Materials). The following sequences are acquired: MEGA-PRESS (48), BOLD fMRI (TR: 2,000 ms, TE: 25 ms, matrix 84 × 84, FOV 210 mm, number of slices: 42, slice thickness: 2.5 mm, voxel: 2.5 mm) and perfusion (3D GRASE Pseudo-Continuous Arterial Spin Labeling, pCASL; TR: 4,300 ms, TE: 36.76 ms, bandwidth: 2,604 Hz/Px, label time 1,500 ms, post-labeling delay: 2,000 ms). In addition, before RPSS a high resolution T1 volumetric (voxel size: 0.5 × 0.5 × 1 mm^3^, matrix size: 256 × 256, field of view: 256 × 256 mm^2^, TR: 2,500 ms, TE: 3.47 ms, TI: 1,100 ms, flip angle: 7 degrees) and after, DWI (voxel size: 2 mm, isotropic; TR:10,200 ms; TE:103 ms) and GRE (voxel size: 0.9 mm × 0.9 mm × 5 mm, matrix size: 256 × 192, field of view: 240 mm, TR: 250 ms, TE:15 ms) are acquired.

The GABA spectroscopy data are collected with MEGA-PRESS (30 × 30 × 30 mm^3^ voxel, TR 2,000 ms, TE 68 ms; water suppression band set to 4.7 ppm, and an editing band alternated between 1.9 ppm and 7.5 ppm in even and odd acquisitions; 192 averages-−96 “edit off” and 96 “edit on”) and a water reference scan using the MEGA-PRESS sequence without MEGA water suppression. Data are collected first from the right and then from the left cerebral hemispheres. Therefore, the ipsilesional and contralesional hemispheres are assessed. In each hemisphere, the region of interest is centered on the “hand knob” in the primary motor cortex (49). Patients are instructed to keep their eyes closed during imaging acquisition.

During fMRI scans, six blocks of finger tapping followed by rest are performed. Before being scanned, subjects practice a self-paced rhythmic finger tapping task consisting of 6 epochs of 30 s of finger tapping alternated with epochs of 30 s rest. Patients are instructed to keep their eyes open. Performance of finger tapping is not one of the inclusion criteria but because patients must be able to perform the JTT in order to be included, only patients with mild upper limb impairments participate in the study. All patients are encouraged to try to perform the task as accurately as possible. It is possible that some patients, despite mild motor impairments, are not able to accurately perform finger tapping. In order to check task performance, finger tapping during fMRI is videotaped. Two researchers review all the videos. Data from patients unable to perform finger tapping are excluded from the analysis.

Sleepiness can potentially influence task performance and GABA levels. Subjects are instructed not to drink alcohol 48 h before the tests, sleep the night before, drink the usual amount of coffee, and do not perform vigorous physical activity on the day of the test. Before MRI (Figure 1), the Epworth Sleepiness Scale is evaluated (50). VAS scores for sleepiness, fatigue, and anxiety (51), blood pressure, and heart rate are assessed before and after MRI.

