**Methods:**

In this multicenter, randomized, parallel-group, proof-of-principle clinical trial with blinded assessment of outcomes, we compare the effects of one session of suprasensory or subsensory RPSS in patients with ischemic or hemorrhagic stroke and upper limb paresis. Clinical assessment and MRI will be performed only once in each subject (either at an early or at a chronic stage). The primary outcome is the change in performance in the Jebsen–Taylor test. Secondary outcomes: hand strength, cerebral blood flow assessed with arterial spin labeling, changes in the blood oxygenation level-dependent (BOLD) effect in ipsilesional and contralesional primary motor cortex (M1) on the left and the right hemispheres assessed with functional MRI (fMRI) during a finger-tapping task performed with the paretic hand, and changes in GABA levels in ipsilesional and contralesional M1 evaluated with spectroscopy. The changes in outcomes will be compared in four groups: suprasensory, early; subsensory, early; suprasensory, chronic; and subsensory, chronic.

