### Participants

The inclusion and exclusion criteria are shown in Table 1. Subjects able to perform at least four of the tasks of the Jebsen–Taylor test (JTT) are included. The JTT scores the time (in seconds) required to perform activities often used in daily living: copying a sentence; turning over cards; picking up small common objects such as coins, bottle-cap, and paper clips; simulated feeding using a spoon; stacking checkers; and moving large light and heavy objects (32, 35).

**Table 1 T1:** Inclusion and exclusion criteria.

**Inclusion criteria**	**Exclusion criteria**
• Age ≥ 18 years • Ischemic or hemorrhagic stroke confirmed by computed tomography or magnetic resonance imaging, between 7 days and 3 months before enrollment (subacute phase), and at least 6 months (chronic phase) • Ability to perform at least 4 of 7 tasks performed in daily life that is part of the Jebsen–Taylor test; • Upper limb paresis contralateral to the lesion	• Inability to provide consent • Anesthesia of the paretic hand • Severe spasticity at the paretic elbow, fist or fingers, defined with a score larger than 3 on the Modified Ashworth Scale • Shoulder pain or join deformity in the paretic limb • Lesions affecting cerebellum, or cerebellar pathways in the brainstem • Uncontrolled psychiatric disease • Neurological diseases such as Parkinson disease or chronic uncontrolled chronic disease such as cancer or cardiac insufficiency • Aphasia or severe cognitive deficit

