### Imaging Data Analysis

#### GABA Spectroscopy

Data processing for the GABA quantification is carried out using Gannet v. 3.1.5, an open-source software coded with MatLab (52). Ratios of GABA levels between the affected and unaffected hemispheres, before and after suprasensory or subsensory RPSS, will be compared (53) in the EARLY and the CHRONIC groups. The pipeline for analysis is shown in Supplementary Materials.

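### GABA is always scanned right hemisphere first but analysed by lesion side, so lesion side fixes acquisition order and should be a factor in the GABA models

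*Protocol article*

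**What the plan says.** Under Imaging Outcomes, the order of GABA acquisition is the same for all patients: "Data are collected first from the right and then from the left cerebral hemispheres". The next sentence draws only a conclusion about coverage: "Therefore, the ipsilesional and contralesional hemispheres are assessed". The same section gives 192 averages per voxel with "TR 2,000 ms, TE 68 ms", asks patients to keep their eyes closed, and notes that sleepiness can influence GABA. Imaging takes place at HIAE, both before and after stimulation: "MRI is performed before and after suprasensory RPSS or subsensory on a 3T Magnetom PRISMA scanner".

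The outcome is defined by lesion, not by anatomical side. The abstract lists "changes in GABA levels in ipsilesional and contralesional M1 evaluated with spectroscopy", and the GABA Spectroscopy section states: "Ratios of GABA levels between the affected and unaffected hemispheres, before and after suprasensory or subsensory RPSS, will be compared".

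Eligibility (Table 1) allows a lesion on either side and requires "Upper limb paresis contralateral to the lesion", so side of paresis identifies side of lesion. Side of paresis is one of five stratification factors. The Statistical Analysis section names two factors for the GABA change model, INTERVENTION and GROUP. It also lists baseline GABA in M1 among the possible predictors of behavioural improvement.

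**The concern.** Order is fixed by anatomy and the endpoint by lesion. In right-lesion patients the affected/unaffected ratio is first voxel over second; in left-lesion patients it is second over first. Whatever differs between the first and second acquisition enters the ratio with opposite sign in the two kinds of patient, and the stated model has no term to absorb it.

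The trial looks for a change after one 2-hour session, so time since stimulation may matter. Drowsiness is the other candidate: the later voxel comes after a longer eyes-closed period, and the post-RPSS scan follows two hours of sitting. What is at stake is precision in a small single-centre imaging subset, and some bias if right- and left-lesion patients are spread unevenly over the groups compared.

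**Working it through.** The plan states no figure for this point, so there is none to reproduce. The check has four steps.

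**1. Lag between hemispheres (Imaging Outcomes).** Averages x TR = 192 x 2.0 s = 384 s = 6.4 min. This is a minimum, because the durations of the water reference, voxel placement and shimming are not given. The interval from the end of RPSS to the first voxel is not given either, so first and second are relative terms only.

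**2. What survives the pre-post subtraction.** Write each reading as true level + order effect. One order is stated, so it is taken to apply to both scans.
- Order effect identical before and after RPSS: cancels in the change.
- Stimulation effect that fades or builds during the post-RPSS scan: does not cancel, since it has no counterpart before RPSS.
- Order effect that differs between scans, for example more drowsiness after the 2-hour session: does not cancel.
- Baseline GABA as a predictor: nothing is subtracted, so even a constant order effect stays.

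**3. Possible size of a fade (assumed; the document gives no time course).** Share of the effect lost between first and second voxel at a 6.4 min lag:

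| Assumed time course | Share lost |
|---|---|
| Linear to zero over 60 min | 6.4/60 = 10.7% |
| Linear to zero over 30 min | 6.4/30 = 21.3% |
| Half-life 120 min | 1 - 0.5^(6.4/120) = 3.6% |
| Half-life 60 min | 1 - 0.5^(6.4/60) = 7.1% |
| Half-life 30 min | 1 - 0.5^(6.4/30) = 13.7% |
| Half-life 15 min | 1 - 0.5^(6.4/15) = 25.6% |

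These are losses within one patient. A group contrast is moved only by the imbalance in lesion side. With a 20-point difference in the share of right lesions, the contrast in mean ipsilesional change shifts by 0.20 x 10.7% = 2.1% to 0.20 x 21.3% = 4.3% of the effect under the linear assumptions, and by 0.20 x 3.6% = 0.7% to 0.20 x 25.6% = 5.1% under the half-lives shown.

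**4. How likely such an imbalance is.** The strata are phase 2 x gender 2 x age 3 x side 2 x FMA 2 = 48. HIAE and HCFMUSP together plan 12 x 4 = 48 patients, so 48/48 = 1 per stratum on average, against blocks of 4. A simulation assumed 24 patients per phase, half with right lesions, gender and FMA split evenly, age split 20/65/15, and blocks of 4 within full strata. Within a phase:
- arms differ by 20 points or more in share of right lesions: about 19% of trials;
- the same without stratification: about 31%.

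Phase is not randomised. With 24 per phase and half right lesions in each, EARLY and CHRONIC differ by 20 points or more by chance in about 19% of trials. Imaging is at HIAE only, so the imaging subset may be smaller than assumed here.

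**The case against.** Several arguments on the other side are sound.

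- **Cancellation.** A reader might infer that the fixed order corrupts every GABA change through drift, movement and drowsiness. The documents do not support that: the outcome is a pre-post change and one order is stated, so a constant order effect drops out. This stands, and it narrows the point to the three residual routes above.
- **Stratification.** Lesion side is already a randomisation factor through side of paresis. This stands in part. In the simulation it lowers the chance of a 20-point arm imbalance from about 31% to 19%, but it does nothing for the EARLY versus CHRONIC contrast.
- **Size.** A reader might take a loss of 11% to 21% as the error in the result. That range needs an assumed linear fade over 30 to 60 min and applies within a patient; the shift in a group contrast is far smaller.
- **Scan order.** It is tempting to say the scan should start with the ipsilesional side. That would tie order completely to affected/unaffected, whereas right-first with both lesion sides enrolled partly counterbalances it.
- **No lesion-side comparison is planned**, so the fact that a lesion-side difference could not be separated from scan order harms no stated analysis. This stands.
- **Sleepiness is managed** by instructions, the Epworth scale, and visual analogue ratings before and after MRI. This helps, but ratings at the two ends of the scan cannot separate the first voxel from the second.
- **Covariates may be set elsewhere**, in a SAP or in the supplementary GABA pipeline. That is possible. However, the article does state the model factors for GABA change, and lesion side is not among them.

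**Conclusion.** The point holds in a limited form. From the text alone, acquisition order and a lag of at least 6.4 min are fully determined by lesion side, and the stated GABA model does not account for this. The likely consequence is added variance in the lesion-defined GABA measures. Bias is possible where lesion side is unbalanced, mainly in the unrandomised EARLY versus CHRONIC contrast and to a lesser degree between arms.

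The size cannot be derived from the document, since it gives neither a time course for the GABA response nor a measurement SD. Under the assumed fades, a 20-point imbalance moves a contrast in ipsilesional change by roughly 1% to 5% of the effect. The documents do not support a claim that the GABA results are invalid or that the scan order itself is an error. GABA is a secondary, mechanistic outcome at one centre, and the primary Jebsen-Taylor outcome is unaffected.

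**What to change.** Add lesion side (right/left) as a factor, alongside INTERVENTION and GROUP, in the GABA change models of the Statistical Analysis section, and as a covariate in the regressions that use baseline GABA. Under the current procedure lesion side is equivalent to acquisition order, so the term covers patients already scanned. Lesion side is recorded at baseline and used in randomisation, so no new data are needed. The cost is one degree of freedom per model. The coefficient should not be read as an order effect, because it also carries any true difference between right and left lesions. If a SAP or the supplementary pipeline already includes this term, a sentence saying so is enough.

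Scanning the ipsilesional M1 first is optional. It would hold order constant across the arm and phase comparisons, but it would alias order with affected/unaffected and, if adopted mid-study, would mix orders among left-lesion patients. If it is adopted, record the order for each scan and model order explicitly, because lesion side would no longer stand in for it.
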